**Figure 3 fig3:**
[figure not shown]
Illustration of multiple-instance learning. The red and blue lines indicate bags of heart disease patients and reference subjects. Even though the labels for each instance are not known, for the sake of this example, the plus and minus signs depict time windows where heart disease is present or absent, respectively. The decision boundary is depicted by a dotted circle, where instances within the circle are classified as heart disease, and instances outside the circle are classified as healthy.

Box 1. A simple multiple-instance learning exampleMIL is elaborated with an example in 3 steps.**Initial setup** Under traditional supervised learning, each window must be annotated to train a machine learning model. However, in our MIL setting (Figure 3), only the bag label is known for the entire set of windows related to a subject. A bag label is considered negative if none of the subject’s individual samples are associated with heart disease, indicating that the subject is not affected by it. Conversely, a bag label is positive if a certain amount of the subject’s samples is linked to heart disease.**Learning** The algorithm then learns a model based on the bag-level labels only. The goal of the MIL algorithm is to learn a model that can correctly predict the bag-level labels given the instances in each bag. By training on the bag-level labels, the MIL algorithm can capture patterns and relationships within the data that help identify the presence or absence of heart disease. Note that the decision boundary produced by the model in Figure 3 is not ideally suited for classifying individual windows, which is expected, as it did not use this information. However, if a sufficient number of windows are classified accurately, the correct bag label can still be predicted. This is accomplished during training by aggregating these accurate classifications using methods like majority voting, or by setting a threshold for the minimum number of positively predicted windows needed to assign a positive bag label.**Prediction** Once the model is trained, it can predict the label of a new bag by examining the instances in the bag. If the model predicts that a certain percentage of instances in the bag are positive defined by the threshold, the bag is classified as positive (heart disease) and negative (healthy) otherwise. By analyzing the presence or absence of positive instances within the bag, the MIL algorithm can make predictions on a bag level, providing insights into the subject’s condition.

### Algorithm validation

In our specific setting where the model encounters data from previously unseen subjects without any prior knowledge, we use leave-p-subjects-out cross-validation (LPSOCV). This approach, shown in Figure 4, ensures a more accurate reflection of real-world situations. LPSOCV involves multiple iterations, or folds, during which data from distinct subjects are used for training and validation purposes (ie, the model is validated on data from subjects that the model is not trained on), mitigating observation bias.

**Figure 4 fig4:**
[figure not shown]
Our leave-p-subjects-out cross-validation strategy consists of the following: On the left, cross-validation folds are illustrated using 3 subjects with corresponding subject number. Green and blue represent training and validation subjects, respectively. On the right, a single fold is expanded and additionally illustrates the internal and external test sets. Each row corresponds to a subject, and the dotted squares within each row represent windows. The yellow external test block encompasses entire subjects and their corresponding data points that have not been encountered by the model. Meanwhile, the dark yellow internal test block consists of unobserved data points, representing the final 20% measurements of the time series from subjects already encountered during model development.

Machine learning models are sensitive to the distribution of classes. To mitigate potential bias owing to different class distributions in each fold, we incorporate stratification during the cross-validation process. This ensures that the ratio of nonarrhythmic, atrial fibrillation, and heart failure subjects remains approximately consistent and that the influence of inconsistent class distribution across different folds is minimized.

However, Fitbit time series data exhibit inter-subject variability resulting from individuals’ distinct physical attributes,^10^ making the development of a universally effective model for “new” subjects challenging. In order to examine the effect of inter-subject variability, we will assess the model on 2 distinct test sets. The first is an external test set that consists of subjects not previously encountered, randomly selected to make up 20% of the total subjects, with an equal number from each class. This allows us to evaluate the model’s generalization capabilities. The second test set is an internal one, encompassing the final 20% of data from subjects previously encountered by the model. This segment of data was excluded during the cross-validation phase and serves as a baseline, as it minimizes the influence of inter-subject variability, providing a reliable reference for comparison.

Parameters not directly learned by the machine learning model, such as window parameters, are termed hyperparameters. Since optimal values are typically unknown in advance, multiple options are examined during LPSOCV, and the best-performing one, with the best average performance over all folds, is chosen for the final model; a process known as hyperparameter tuning.

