**Figure 1 fig1:**

Data analysis pipeline for the ME-TIME study. Included participants (image 1) are given a smartwatch (image 2), which is connected to our data acquisition and storage platform (image 3). The resulting data are then preprocessed (image 4) and put into the data-efficient machine learning model (image 5). AF = atrial fibrillation group; HF = heart failure group; Ref = reference group.

Patients will be asked by their treating physician if they may be approached by an investigator to inform them about the study and potential participation. Healthy participants are recruited through local advertising. Anyone that is interested will then receive an information brochure and informed consent form. At least 2 days after the patient’s receipt of the brochure, the research team will call the patient to schedule an appointment. During this visit, the patient submits the signed consent form and will undergo an ECG and blood pressure measurement that will be analyzed by an experienced cardiologist ([name]). Participants can use their own Fitbit and are otherwise provided with a Fitbit Inspire 2 or Fitbit Charge 5 smartwatch. The device type is assigned to a participant at random to prevent device sampling bias. This will also help to investigate the effect of device type on the performance of the final model. A Fitbit account will be created for all participants which will be connected to a custom-built data platform using the Google Cloud Platform. Our platform features a data portal for research staff to easily register or deregister participants by authorizing a connection to their Fitbit data. Data are extracted daily from Fitbits until the observation period ends and can be analyzed either in the cloud or locally.

All participants will be asked to fill out a survey regarding their health. All participants are monitored for a period of 3 months. After written consent from the 200 subjects, heart rate, step counter, and sleep time series data are extracted from the data platform. Clinical metadata such as age, height, weight, blood pressure at baseline, health survey, and medication use are saved in the Castor (Ciwit BV, Amsterdam, The Netherlands) electronic database.

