### Data characteristics and preparation

The data first undergoes a process involving resampling and artifact removal. In our experience with Fitbit smartwatches, the heart rate is nonuniformly sampled, with a prevalent rate of 0.2 Hz. Therefore, the heart rate is resampled to once per 5 seconds. The step counter is sampled once per minute.

Artifacts involving samples with numerous consecutive constant values are removed, if more than 12 consecutive constant values (equivalent to 1 minute of heart rate samples) are detected. This 1-minute threshold was chosen based on visual inspection, which revealed that heart rate patterns typically occur in the order of minutes, often spanning 10–20 minutes. For sequences with fewer than 12 consecutive missing values, linear interpolation is applied. From the cleaned time series, smaller segments, denoted as windows, are extracted and employed as input for a machine learning model. This process involves a sliding window and windows containing time gaps are excluded. Windows have 2 design considerations: the window size, which determines the number of samples within a window and defines its dimensionality, and the stride, which establishes the step size dictating the shift between windows.

Although the cardiovascular condition of each subject is known, it is unknown in which specific windows these conditions manifest themselves. This is owing to the paroxysmal nature of atrial fibrillation and the variable symptoms of heart failure, which can be influenced by factors like medication adjustments, dietary changes, and the disease’s progressive course. In other words, the subject label is known, but the individual window labels are unknown. This is visually represented in Figure 2a, where the subject label is depicted by the blue/red colors and the unknown window labels are indicated by black dotted lines.

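### The internal test set holds only the last fifth of each seen subject's recording and the external set holds whole recordings, so their difference cannot be attributed to unseen subjects alone

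*Protocol article*

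**What the plan says.** The Algorithm validation section gives the purpose of the comparison: "In order to examine the effect of inter-subject variability, we will assess the model on 2 distinct test sets".

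- **External set.** The Figure 4 caption says: "The yellow external test block encompasses entire subjects and their corresponding data points that have not been encountered by the model". The subjects are "randomly selected to make up 20% of the total subjects, with an equal number from each class".
- **Internal set.** The text says: "The second test set is an internal one, encompassing the final 20% of data from subjects previously encountered by the model". The caption agrees: "representing the final 20% measurements of the time series from subjects already encountered during model development". This segment is kept out of cross-validation. The article says that it "serves as a baseline, as it minimizes the influence of inter-subject variability, providing a reliable reference for comparison".

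Three other statements matter here. Under Study design and data collection: "All participants are monitored for a period of 3 months". Under Planned machine learning approach, the main aim at testing is one predicted outcome per subject, obtained from a bag of windows. Under Data characteristics and preparation, the article explains why it is not known which windows show disease: "This is owing to the paroxysmal nature of atrial fibrillation and the variable symptoms of heart failure". It adds medication changes, diet and progression as influences on heart failure.

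The article nowhere limits external subjects to a matching segment or equalises observation time between the sets.

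**The concern.** The comparison is meant to isolate one factor: whether the model has met the subject before. As written, the two sets also differ in two other ways.

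1. **Length.** A subject-level prediction in the external set can draw on about five times as much recording.
2. **Period.** The internal set samples late wear only; the external set covers early and late wear.

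Neither is neutral under the plan's own model, in which a subject's label comes from aggregating windows and disease shows in some windows and not in others. Part of any internal-external difference could arise with no inter-subject effect, and a real effect could be masked or exaggerated. The Discussion names the influence of inter-subject variability as something the study aims to examine, so the contrast carries a stated aim.

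**Working it through.** The article gives no figure for this contrast, so there is nothing of its own to reproduce.

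**Step 1. Observation time.** Inputs: 3 months (Study design and data collection), taken as 91 days; 20% and whole recordings (Algorithm validation and Figure 4 caption). Assumption: similar recording length and wear across subjects.

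- Internal: 0.20 × 91 = 18.2 days, after the first 72.8 days.
- External: 91 days.
- Ratio: 91 / 18.2 = 5.0. In weeks: 13.0 against 2.6.

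If a bag is a subject's available recording, the bag threshold is tuned on about 72.8 days. It is then applied to internal bags 4 times shorter (72.8 / 18.2) and external bags 1.25 times longer (91 / 72.8). The reference set is then further from the tuning conditions than the set it is a reference for.

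**Step 2. Does length alone move the result?** The article gives the bag rule as a number of positive windows (Planned machine learning approach) and as a percentage (Box 1), so both are tried. Assumptions: 90 days of independent 1-hour windows (2160 external, 432 internal, 1728 for tuning); window-level accuracy identical in both sets; 1% of windows positive in a healthy subject and 6% in an AF subject; threshold tuned to about 95% specificity, which gives 25 of 1728 windows.

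| Rule | Specificity, external | Specificity, internal | Sensitivity, external | Sensitivity, internal |
|---|---|---|---|---|
| Count: at least 25 | 0.74 | 1.00 | 1.00 | 0.60 |
| Percentage: at least 25/1728 = 1.45% | 0.98 | 0.85 | 1.00 | 1.00 |

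The sets differ although no inter-subject effect was built in. The specificity gap changes sign between the two rules.

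**Step 3. Intermittent episodes.** Assume Poisson episodes at rate r per 30.4 days and a rule under which one episode makes the bag positive. Then P(at least one) = 1 − exp(−r × days / 30.4).

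| r per month | Internal, 18.2 days | External, 91 days |
|---|---|---|
| 0.5 | 26% | 78% |
| 1 | 45% | 95% |
| 2 | 70% | 99.7% |
| 4 | 91% | 100% |

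Now use a percentage rule, assuming 12-hour episodes, r = 0.5 and a 2% threshold.

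- Internal: 2% of 18.2 days is 8.7 hours. One episode suffices (12 / 436.8 hours = 2.7%). With mean 0.30, P(at least 1) = 26%.
- External: 2% of 91 days is 43.7 hours. Four episodes are needed. With mean 1.50, P(at least 4) = 7%.

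The sensitivity gap reverses. All rates, durations and thresholds in steps 2 and 3 are assumptions; the article gives none.

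**Step 4. Class mix.** The external set is 0.20 × 200 = 40 subjects in equal numbers per class. Since 40 / 3 = 13.3, take 13 each. That leaves 87, 37 and 37 of 161 subjects for the internal set (54%, 23%, 23%) against one third each externally. A pooled metric would differ for this reason too, even after length and period were matched.

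**The case against.** **A reader might infer that the short internal bags lower internal sensitivity, by up to about 50 points in paroxysmal AF.** The documents do not support this. The figures behind it (26% against 78%) need a rule under which one episode makes a bag positive. The plan moves away from such a rule by requiring a tuned number of positive windows, and Box 1 uses a percentage. Under a percentage rule the expected positive fraction does not depend on bag length; only its spread does, and step 3 shows that the gap can reverse.

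**The bag length at testing is not stated.** The article's one worked multiple-instance analysis forms weekly bags. If the final model is scored per weekly bag, bag length is equal in both sets and the length argument falls away at bag level. This stands as a limit. However, the stated target is one outcome per subject, which would still rest on about 13 weekly bags against 2.6, and the period would still differ.

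**The scope of episode capture is narrow.** It concerns paroxysmal AF, whose share is not given; the AF group also includes persistent and permanent AF. This stands. The distortion from late-only sampling, and any effect in heart failure, cannot be quantified from the article.

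**The caption speaks of measurements, not days, and windows with gaps are dropped.** Correct: the five-fold ratio is approximate for any one subject.

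**A temporal hold-out in seen subjects is ordinary practice, and an article leaves detail to the full protocol.** The hold-out is not the difficulty. The article defines both sets and itself calls the shorter, later one a reliable reference, so the mismatch is stated and not merely left open.

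**Conclusion.** The concern holds as a matter of attribution. Read as written, the contrast combines subject novelty with about a five-fold difference in observation time (91 against 18 days, assuming similar wear) and with late-only sampling in the internal set. It cannot by itself show the effect of inter-subject variability.

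No size or direction for the resulting distortion can be asserted. Both depend on whether the bag rule is a count or a percentage, on the bag length and on the mix of AF types. The figures in steps 2 and 3 show only that the sets can differ, in either direction, without an inter-subject effect. Performance of the model in new subjects, estimated on whole external recordings, is not called into question by this point.

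**What to change.** Keep the full-length external result as the estimate of generalisation. In addition:

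1. Score the frozen model on the final 20% of each external subject's recording, with the same bag length and bag rule as for the internal set.
2. Report both sets per class, or under the same class weights, because the external set has equal numbers per class and the internal set does not.
3. Base the inter-subject-variability conclusion on this matched contrast, and say so in the Algorithm validation section, together with the bag length used.

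The cost is one extra scoring run on data already held and a sentence or two of text. External performance in the matched contrast will be estimated less precisely, because each subject contributes about a fifth of the recording. The main external estimate is unchanged.

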### Planned machine learning approach

Our planned machine learning approach is tailored to operate in this setting through a 2-stage process. To learn informative patterns/features directly from the input data, despite the lack of labeled windows, the first stage involves using self-supervised learning. A commonly used self-supervised learning technique involves compressing the input windows to a lower-dimensional representation and then reconstructing the original input from this compact representation, as depicted in Figure 2b.^7^^,^^8^ Instead of reconstruction, another technique is to forecast future time points of the input data.^9^ The second stage involves multiple-instance learning (MIL). MIL, depicted in Figure 3 and more elaborately explained in Box 1, is suitable for data where a single prediction is made collectively on a group of samples (known as a “bag”) instead of predicting on individual samples (known as “instances”). MIL techniques align well with our time series data, where during the training phase only 1 label related to the subject (bag label) is known while the individual labels of the compressed windows (instance labels) remain unknown. In the testing phase the primary objective is to predict 1 clinical outcome for each subject. The key concept in MIL is that each bag of instances is labeled as positive (heart disease) if it contains a certain amount of positive instances and negative (healthy) if it contains no positive instances (only negative instances). Although traditional MIL approaches often classify a bag as positive even with just 1 positive instance, we aim to minimize false-positives by setting a threshold on the number of positive instances required to label a bag as positive. This threshold will be determined through hyperparameter tuning. Thus, instead of learning a model that predicts the cardiovascular outcome of individual instances, we are learning a model that predicts the outcome of a bag of instances.

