**Figure 5 fig5:**
[figure not shown]
Visualization of heart rate windows (upper image) and step windows (lower image) of 6 subjects. Each window has data of 1 hour (720 time points for heart rate, 60 for steps, respectively). Each high-dimensional window is mapped to a 2-dimensional (2D) location using UMAP.^11^ The contour curves illustrate the distribution of the 2D UMAP samples for each subject, with each color representing 1 of the 6 subjects.

When there is little overlap between subjects, finding a shared pattern among them becomes challenging, making it difficult for a model to learn. As a result, the performance of a machine learning model could be impacted as, during testing, a subject can significantly deviate from the subjects on which the model was trained.

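### The internal test set is not a reliable reference for inter-subject variability: each subject's label is constant and already seen in training, so recognising the subject can raise the score without any disease signal

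*Protocol article*

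**What the plan says.** The Algorithm validation section of the Protocol article sets up two test sets for a stated purpose: "In order to examine the effect of inter-subject variability, we will assess the model on 2 distinct test sets".

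- **External set:** unseen subjects, "randomly selected to make up 20% of the total subjects, with an equal number from each class". Evaluation of generalization is assigned to this set.
- **Internal set:** "encompassing the final 20% of data from subjects previously encountered by the model". The Figure 4 caption describes the same block as "representing the final 20% measurements of the time series from subjects already encountered during model development". The text adds that it "serves as a baseline, as it minimizes the influence of inter-subject variability, providing a reliable reference for comparison".

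Two earlier sections fix the level of the label. Data characteristics and preparation says that "the subject label is known, but the individual window labels are unknown". Planned machine learning approach says that during training "only 1 label related to the subject (bag label) is known".

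The Abstract and the Results both report considerable variability between subjects. On Figure 5, the Results comment: "When there is little overlap between subjects, finding a shared pattern among them becomes challenging".

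**The concern.** For every subject in the internal set, the right answer has already been given to the model, attached to that person's earlier data. If people can be told apart from their heart rate and step patterns, identifying the person is enough to return the class. Variability between subjects is what makes people identifiable. It can therefore enter the internal score as an advantage, and the claim that the set minimizes its influence does not follow.

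What is at stake is the contrast that the two sets were built to provide. A large gap could mean that a real disease pattern transfers poorly to new people. It could equally mean that there is little disease pattern and the model has learned who is who. These readings lead to different next steps, and the design as described cannot tell them apart.

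**Working it through.** **Logic.** Let S be the subject and Y = g(S) the class, constant within a subject.

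- In the internal set, g(S) was supplied in training for every S. A rule that identifies S and returns g(S) is right whenever the identification is right, with or without a disease signal.
- In the external set, S was never seen, so the same rule has nothing to look up and scores at chance.
- Hence: internal minus external = (loss from subject shift) + (gain from recognition). There is one observed difference and two unknown parts.

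**Size.** The article states no performance figure for the internal set, so there is nothing to reproduce. The mechanism was simulated with no disease signal.

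Inputs from the article:
- Classes 100 / 50 / 50.
- Three months of monitoring, about 13 weeks; one bag per week, as in the preliminary MILES analysis.
- 80/20 cut: 0.8 × 13 = 10.4, so 10 weeks for training and 3 for the internal test.
- External set: 0.2 × 200 = 40 and 40 / 3 = 13.3, so 13 per class, 39 in all. This leaves 200 − 39 = 161 development subjects (87 / 37 / 37).

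Assumptions, because the article gives none:
- Gaussian features x = μ(subject) + e, with var(μ) = ρ and var(e) = 1 − ρ; ρ is the between-subject share of variance, taken from 0 to 0.7.
- 8 or 16 dimensions.
- Class-weighted 10-nearest-neighbour vote, pooled to one prediction per subject; 20 replicates.

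Measure: balanced accuracy = (1/3) × sum over classes of the proportion correct in that class; chance = 0.33.

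| ρ | 8 dim: internal / external | 16 dim: internal / external |
|---|---|---|
| 0 | 0.322 / 0.331 | 0.343 / 0.315 |
| 0.1 | 0.348 / 0.321 | 0.343 / 0.337 |
| 0.3 | 0.398 / 0.356 | 0.489 / 0.321 |
| 0.5 | 0.555 / 0.295 | 0.765 / 0.349 |
| 0.7 | 0.780 / 0.305 | 0.972 / 0.350 |

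The external values scatter about 0.33. Their simulation standard error is about √(0.333 × 0.667 / 39) / √20 = 0.017.

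**Does a real signal show?** A true class shift of 0.5 SD at ρ = 0.7 in 8 dimensions moved the external score from 0.305 to 0.399, but the internal score only from 0.780 to 0.785. With 16 dimensions the internal score went from 0.972 to 0.978. When recognition is strong, the internal score says little about disease.

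**Other classifiers.** At ρ = 0.5 with no signal, separate runs gave internal balanced accuracy of 0.44 to 0.53 for linear models and 0.49 to 0.76 for instance-similarity models of the MILES kind. External accuracy was 0.29 to 0.38. The inflation is smaller than for nearest neighbours in some runs, but it is present.

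**Class mix.** The internal set is 87/161 = 54% reference and 37/161 = 23% for each disease group; the external set is one third each. Always predicting reference would score 54% against 33% in raw accuracy, so only a class-balanced measure can be compared across the two sets.

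**The case against.** The case on the other side is substantial, and much of it stands.

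- **Generalization does not rest on the internal set.** It is assigned to the external set. Cross-validation is by subject and hyperparameters are chosen on its folds, so pure memorisation earns nothing at selection. This stands. A reader might infer that the study's performance claims are contaminated; they are not.
- **The size depends on the classifier.** This stands. In a two-class version with random labels (160 subjects, 10 features, chance 0.50), nearest neighbours rose from about 0.54 to 0.88 as ρ went from 0.1 to 0.5. A linear model stayed at 0.58 to 0.61 and did not rise with ρ over 0.1 to 0.7. The planned model is neither of these. A reader might infer that the gap will mostly measure memorisation, or that an internal score near the top of the range is to be expected. The article gives no variance share, signal strength or final model that would support either.
- **The Figure 5 comment is conditional.** It says what follows when overlap is small. It does not say that overlap is small, and the figure covers six subjects. The claim of large variability rests on the section heading and the Abstract, without a number.
- **Shared samples at the 80/20 cut.** A reader might suspect that sliding windows straddle the cut. The article describes a cut in measurements that were held out of cross-validation, and Figure 4 is not shown, so this is not supported.
- **A same-subject comparator does remove the shift between training and test subjects.** That is a fair sense of minimizing inter-subject variability. But removing the shift also brings in recognition, and the article describes no control for it. This part of the objection does not rescue the claim of a reliable reference.

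**Conclusion.** The point holds as one about interpretation. The article gives a positive rationale for the internal set, and that rationale does not follow from its own design: labels are constant within subjects and were supplied in training. An internal score above chance needs no disease signal, and the internal-external gap cannot by itself show the effect of inter-subject variability.

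The mechanism requires only that subjects be distinguishable, which the article asserts in general terms; at ρ = 0 the inflation vanishes. Its magnitude rests on assumed variance shares, dimensions and classifiers. Across these, the null internal score ran from chance to roughly 0.5 for linear models and to 0.76 to 0.98 for nearest-neighbour or instance-similarity models. That is a range of possibilities and not a forecast for the planned model.

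**What to change.** 1. Permute class labels across development subjects, keeping each subject's label constant over time. Refit the multiple-instance stage at the chosen hyperparameters and score the internal set. The self-supervised stage uses no class labels and need not be refitted. Repeat as often as compute allows: 200 permutations if feasible, 20 if not.
2. Report the internal score beside this null distribution, on a class-balanced measure, and do the same for the external score. Do not treat internal minus null as an exact disease component: near the ceiling the two parts do not add.
3. At minimum, if the permutations are not run, describe the internal score as an optimistic same-subject figure, drop the statement that it is a reliable reference, and do not read the internal-external gap as the effect of inter-subject variability.

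The cost is some extra compute for steps 1 and 2, or wording alone for step 3. No new data or participants are needed. The internal figure will look less favourable. With 62 of 200 subjects included at the time of the article, the change can be made before the final analysis.
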